## Abstract

**Background:**

Multimorbidity (MM) burdens individuals and healthcare systems, since it increases polypharmacy, dependency, hospital admissions, healthcare costs, and mortality. Several attempts have been made to determine an operational definition of MM and to quantify its severity. However, the lack of knowledge regarding its pathophysiology prevented the estimation of its severity in terms of outcomes. Polypharmacy and functional impairment are associated with MM. However, it is unclear how inappropriate drug decision-making could affect both conditions. In this context, promising circulating biomarkers and DNA methylation tools have been proposed as potential mortality predictors for multiple age-related diseases. We hypothesize that a comprehensive characterization of patients with MM that includes the measure of epigenetic and selected circulating biomarkers in the medical history, in addition to the functional capacity, could improve the prognosis of their long-term mortality.

**Methods:**

This monocentric retrospective observational study was conducted as part of a project funded by the Italian Ministry of Health titled “imProving the pROgnostic value of MultimOrbidity through the inTegration of selected biomarkErs to the comprehensive geRiatric Assessment (PROMOTERA).” This study will examine the methylation levels of thousands of CpG sites and the levels of selected circulating biomarkers in the blood and plasma samples of older hospitalized patients with MM (*n* = 1,070, age ≥ 65 years) recruited by the Reportage Project between 2011 and 2019. Multiple statistical approaches will be utilized to integrate newly measured biomarkers into clinical, demographic, and functional data, thus improving the prediction of mortality for up to 10 years.

**Discussion:**

This study's results are expected to: (i) identify the clinical, biological, demographic, and functional factors associated with distinct patterns of MM; (ii) improve the prognostic accuracy of MM patterns in relation to death, hospitalization-related outcomes, and onset of new comorbidities; (iii) define the epigenetic signatures of MM; (iv) construct multidimensional algorithms to predict negative health outcomes in both the overall population and specific disease and functional patterns; and (v) expand our understanding of the mechanisms underlying the pathophysiology of MM.

## Introduction

The number of people with multiple diseases, i.e., multimorbidity (MM), is expected to increase as a result of aging populations and a rise in long-term ailments. MM burdens individuals (65% of adults aged 65–84 years and 82% of those aged 85+ years) and healthcare systems due to the fact that it increases polypharmacy, hospital admissions, healthcare costs, dependency, and institutionalization (1–5). The association between MM and mortality is being investigated as certain studies have revealed a higher risk of death among older adults with MM compared to those without diseases (6, 7), although other studies found no differences (8, 9). The UK Academy of Medical Sciences has deemed it a research priority to reduce the burden of MM, thereby improving patients' quality of life and ensuring the healthcare system's sustainability (10).

One of the consequences of MM is the use of too many medications. This situation, known as polypharmacy, is typically defined as the concurrent intake of 5 or more drugs by a single individual. The prevalence of this condition in the older population grows with age and varies between 10 and 90%, depending on age group, definition used, healthcare, and the study's geographical setting (11, 12). In Italy, 30.3% of 2,057 participants (60% female; mean age 81.7 years) who visited a geriatric hospital emergency department were taking 6–9 drugs concomitantly, and 17.8% of the patients (13) presented with excessive polypharmacy (≥ 10 drugs). In a population of 319,185 Korean adults aged 65 and older, the prevalence of polypharmacy (≥ 6 medications) was estimated to be 86.4%, with 44.9% having excessive polypharmacy (≥ 11 medications) and 3.0% taking ≥ 21 medications (14). Polypharmacy increases the likelihood of adverse reactions, including drug-drug and drug-disease interactions (15), and is associated with a higher risk of inappropriate prescribing (12). However, it is unclear which unsuitable medication(s) could induce the onset of new comorbidities in older adults, consequently contributing to the severity of MM.

In contrast, substantial evidence has been presented on the relationship between MM and functional impairment (3, 16, 17). On the one hand, it has been found that the accumulation of chronic diseases may lead to functional impairment (16, 18). On the other, functional decline has been found to be associated with a higher risk of developing multiple chronic diseases, consequently increasing the severity and MM burden (3, 19). It has also been suggested that functional decline in older hospitalized patients may be a stronger predictor of poor outcomes than MM (3, 17, 20–22). Despite all the evidence, it is still unclear how these factors interact with one another and how polypharmacy may impact both.

Several studies have provided solid evidence that it is not merely by accident that chronic diseases may coexist (23–26). Both clinical experience and epidemiological research suggests that diseases often co-occur in an individual according to specific patterns (27, 28). However, no consensus has been reached on how these classifications can be applied to an operational definition to measure MM.

Several attempts have been made to develop a concise measure of MM and quantify its severity (29). However, a dearth of knowledge regarding its pathophysiology prevented the estimation of its severity in terms of outcomes. In order to bridge this gap, weighted disease measures, such as the Charlson Comorbidity Index (30), have been used to define the impact of multiple combinations of health/disease conditions on multiple outcomes, including mortality, quality of life, and resource utilization. However, the majority of studies aimed at estimating the risk of death in patients with MM by utilizing multiple comorbidity indexes indicated a high risk of bias (29).

In this context, a series of circulating physiological markers, including dehydroepiandrosterone sulfate (DHEAS), interleukin 6 (IL-6), C-reactive protein (CRP), cystatin C (Cyst-C), Alpha-2-macroglobulin (A2M), and soluble receptor for advanced glycation end-products (sRAGE), have been found to be associated with several age-related diseases and MM, indicating a potential clinical application for addressing patients with a higher risk of poor outcomes (31–34).

In addition to circulating biomarkers, DNA methylation patterns, which are associated with healthspan and the early prediction of death (35–38), may serve as powerful tools for elucidating the pathophysiology of MM and improving the estimation of its severity. Given the close association between DNA methylation, gene expression, and chromatin accessibility, a network analysis-based approach can be applied to identify several altered pathways that are enriched for disease-related changes (39).

The network medicine approach, which integrates big omics, imaging data, and clinical information, seeks to identify pathological interacting genes and proteins, revolutionizing disease knowledge and shifting the understanding of pathogenic phenomena from a reductionist to a holistic perspective (40).

Understanding the mechanisms of disease and comorbidity development, breaking them down into clusters, and disentangling the epigenetic and actionable components using a network medicine approach is of utter importance from a public health perspective. Currently, epigenetics combined with an innovative systems biology approach is useful for personalized coronary heart disease therapy (41). Furthermore, unlike DNA variants, epigenetic modifications are potentially pharmacologically reversible (42). This is why exploring DNA methylation patterns could: (i) highlight the altered mechanisms underlying MM and functional impairment; and (ii) identify treatments that may be implicated in the onset of new comorbidities or functional decline.

DNA methylation patterns include epigenetic clocks. These represent mathematical models that leverage the variability of a well-defined set of DNA methylation markers (CpG sites) to accurately predict all-cause mortality in later life (36). Multiple studies have demonstrated that epigenetic clocks can represent promising prognostic biomarkers for several diseases, including cardiovascular diseases (43), dementia (44), diabetes (45), and cancer (46), in addition to functional impairment (36) and frailty (47). However, no longitudinal studies have examined the alterations in DNA methylation status in relation to the onset of multiple comorbidities in older adults, with or without functional impairment, and their relationship with polypharmacy.

We hypothesize that a comprehensive characterization of patients with MM, by integrating the assessment of selected circulating and epigenetic biomarkers with the medical history, in addition to an assessment of functional capacity, could improve the long-term mortality prediction of these patients.

### Objectives

#### Primary objective

The main objective of this study is to evaluate the performance of the epigenetic clock expressed as *epigenetic age acceleration (epigenetic clock age–chronological age)* in predicting all-cause mortality in a cohort of MM older patients.

#### Secondary objectives

The study of demographic, clinical, and functional variables in relation to mortality risk and rehospitalization rate after a 10-year follow-up.Evaluation of MM-cluster patient classification in relation to mortality risk and rehospitalization rate after a 10-year follow-up.The assessment of selected plasma proteins, including hsCRP, IL6, A2M, DHEAS, sRAGE, and Cys-C, in relation to clinical, biological, and functional outcomes.

Evaluation of *epigenetic age acceleration (epigenetic clock age–chronological age)* in relation to: (a) anthropometric parameters; (b) multiple patterns of MM; (c) disease distribution among patients; (d) functional status of the patients [Activities of Daily Living (48) and Cognitive Performance Scale (49) scores]; (e) hospitalization rate; (g) routine biological parameters; and (h) onset of new comorbidities related to the use of drugs in the context of polypharmacy.

## Materials and methods

### Study design

This monocentric retrospective observational study was conducted as part of a project funded by the Italian Ministry of Health (Grant No. GR-2019-12368606) titled “imProving the pROgnostic value of MultimOrbidity through the inTegration of selected biomarkErs to the comprehensive geRiatric Assessment (PROMOTERA).”

The PROMOTERA study aims to identify promising biomarkers of healthspan and mortality, such as selected circulating proteins and several DNA methylation biomarkers in the plasma and blood samples of hospitalized older patients recruited by the Reportage project (Trial registration number: NCT01397682; July 19, 2011). The Reportage project is (50) an ongoing prospective observational study involving older patients consecutively admitted to acute care wards in INRCA research hospitals located in the Italian cities of Ancona, Fermo, Cosenza, and Casatenovo. The project began in September 2011 with the aim of creating a large data repository on demographics, comprehensive geriatric assessments, clinical and diagnostic information, and molecular and biological data on older adults receiving acute care. This study included patients who were recruited until 2019. Potential participants were screened for eligibility after they were provided with information describing the study. Eligibility criteria included: age ≥ 65 years, admission to one of the INRCA research hospitals, and written informed consent. In the case of a participant's cognitive decline or impaired judgment, a proxy (relative or caregiver) was requested to give their additional consent. The absence of informed consent from the patient or caregiver (50) resulted in the participant's exclusion from the study. Baseline data were collected for each patient within the first 24 h of hospital admission. Baseline data were incorporated into a minimum data set comprising demographic information, multidimensional geriatric assessment data, clinical, biological, and diagnostic information routinely collected during hospitalization, also utilizing the interRAI Acute Care Instrument (51). Moreover, the Reportage dataset contained information on drug intake (prior to admission, during hospitalization, and at discharge) and diagnostic and treatment procedures performed during hospitalization (including information from X-rays, computerized tomography, ultrasounds, electrocardiograms, magnetic resonance imaging, etc.). The multidimensional geriatric assessment was repeated within 24 h prior to discharge. Blood samples were taken within 24 h of admission and stored at −80°C. A separate and detailed data sheet was used to collect data regarding *ad hoc* investigations to identify biological markers.

The PROMOTERA project aims to update follow-up information on the survival status of hospitalized Reportage Project patients for up to 10 years. It will also incorporate clinical, demographic, and functional data (already available from the Reportage project) with circulating and epigenetic biomarkers, thus improving the prognostic accuracy of patients with MM.

The Reportage project's protocol, recruitment, and informed consents have already been published (50) and approved by the Ethics Committee of the Italian National Institute of Health and Sciences on Aging (CE INRCA 20031, 04/02/2021). The approved PROMOTERA protocol includes DNA analyses on blood samples from the Reportage Project. Blood samples from the Reportage project are stored at −80° C in the biobank (BioGer) of the National Institute of Health and Sciences on Aging IRCCS-INRCA of Ancona.

The project design involves a multi-phase approach (Figure 1).

**Figure 1 F1:**
[figure not shown]
Flowchart of the experimental design.

### Phase I: Follow-up update

Follow-up information on the date of death will be provided for all Reportage project patients for up to 10 years.

### Phase II: Patient selection

One thousand and seventy hospitalized older adults will be randomly selected from the Reportage database on the basis of the following inclusion criteria:

- Age ≥ 65 years.- Clinical records: two or more of the following conditions on an ongoing basis (present in at least 5% of the overall population): heart attack/myocardial infarction, cerebrovascular disease (CVD), dementia, chronic kidney disease (CKD), hypertension, dyslipidemia, ischemic cardiomyopathy, stroke, PAD, chronic obstructive pulmonary disease (COPD), diabetes, cancer, Parkinson's disease, heart failure, atrial fibrillation, anemia, deafness, hip fracture, thyroid dysfunction, asthma, depression, migraine, eczema/dermatitis, irritable bowel syndrome, osteoporosis, anxiety/panic attacks, rheumatoid arthritis, glaucoma, ear/vestibular disorders, epilepsy, chronic sinusitis, tuberculosis, meningitis, multiple sclerosis, bronchiectasis, prostate problems, schizophrenia, hepatitis, liver failure/cirrhosis, and inflammatory bowel disease.- Availability of blood and plasma samples at the IRCCS-INRCA: buffy coat and plasma samples (withdrawn at baseline) stored at −80°C.- Availability of information from baseline to 10 years of follow-up: death, hospitalization, clinical records, functional status, routine laboratory parameters, onset of new comorbidities after the first discharge, and drug intake.

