#### Clinical variables

The objective examination includes blood pressure, heart rate, and anthropometric variables (body mass index, BMI). A thorough clinical history was carefully compiled by trained physicians. Diagnoses were coded using the International Classification of Diseases, 10^th^ Edition (ICD10) (54) and the coding of medications was carried out by means of the Anatomical Therapeutical Chemical Classification System (ATC) (55).

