In order to reduce the complexity of MM, a dimensionality reduction approach will be performed by clustering patients into a few groups on the basis of the most frequent diagnoses at baseline for each stratum in order to obtain a classification of patients according to an MM pattern. The risk analysis will be repeated for each MM pattern. The association between the epigenetic clock and MM patterns will be determined by means of a Generalized Linear Model. Multiple adjusted models will be developed to consider each possible covariate that could influence the significance of the results and to identify independent variables linked to primary and secondary outcomes. Survival analysis with Kaplan Meier estimates will be performed to assess and compare survival over time among the clusters (Log-Rank test). Cox proportional hazards models will be used to assess and compare survival-time outcomes in each cluster in the presence of possible confounders. Several network medicine-based approaches will be developed in order to build the Human Interactomes and Disease Networks (58). Finally, we will investigate the additive effect of the epigenetic clock on the predictive ability of MM patterns. Changes in Harrell's C and the categorical Net Reclassification Index (NRI) will be calculated with 1,000 bootstrap samples to estimate the 95% CI. A two-tailed *p*-value of < 0.05 will be considered statistically significant. The Bonferroni correction for multiple comparisons will be applied to control for the risk of false-positive results. Statistical analyses will be conducted using the Stata 15.1 Software Package for Windows (Stata Corp, College Station, TX).

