### Sample size

The sample size was calculated on the basis of the primary objective (the association between the epigenetic clocks' Δage and mortality). For this reason, we planned to include 1,070 samples of individuals from the Reportage Project. This sample was obtained by setting α = 0.05, β = 0.2, and using a Hazard ratio = 1.23, a 10-year follow-up period, and a median survival time of 6.2 years for patients whose Δage was not expected to increase. This sample size is also in line with other study populations in which the prognostic value of several epigenetic clocks were assessed (36). This sample will enable the detection of significant associations between epigenetic clock Δage and mortality during the 10-year follow-up period.

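### The entry list counts stroke and cerebrovascular disease as two conditions, so one disease can meet the multimorbidity criterion and could create an artefactual cluster

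*Protocol article*

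**What the plan says.** Under Phase II: Patient selection, a patient needs "two or more of the following conditions on an ongoing basis (present in at least 5% of the overall population"). The list that follows has 40 entries and includes "heart attack/myocardial infarction, cerebrovascular disease (CVD), dementia, chronic kidney disease (CKD), hypertension, dyslipidemia, ischemic cardiomyopathy, stroke, PAD". Cerebrovascular disease and stroke are therefore separate entries, as are myocardial infarction and ischemic cardiomyopathy. No rule for combining related entries accompanies the list.

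The Introduction equates multimorbidity with having more than one disease: "The number of people with multiple diseases, i.e., multimorbidity (MM").

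The Statistical analysis section plans "clustering patients into a few groups on the basis of the most frequent diagnoses at baseline". It does not say that the Phase II entries are the clustering variables. Under Clinical variables the article states the coding system ("Diagnoses were coded using the International Classification of Diseases, 10"th Edition) but not how codes map to list entries.

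The resulting groups serve a secondary objective ("Evaluation of MM-cluster patient classification in relation to mortality risk and rehospitalization rate after a 10-year follow-up"). They are also used for the association of the epigenetic clock with multimorbidity patterns and for the clock's added predictive value over those patterns.

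**The concern.** A count of two is meant to show two diseases. When one entry is a subtype of another, a single disease can reach two, and the criterion no longer guarantees the construct it is meant to select.

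The second consequence is potentially larger. The Introduction rests the case for multimorbidity patterns on chronic diseases occurring together more than by chance. A subtype and its parent category occur together by definition. If both are clustering inputs, the algorithm can form a group around that pair. The study would then report the prognosis of stroke under the name of a multimorbidity pattern. That result would carry into the survival comparisons between clusters, the association of Δage with pattern, and the changes in Harrell's C and the reclassification index.

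**Working it through.** **1. The plan's own figure.** Inputs from the Sample size section: "setting α = 0.05, β = 0.2, and using a Hazard ratio = 1.23, a 10-year follow-up period", and a reference median survival of 6.2 years. The test is two-sided according to the Statistical analysis section. A 1:1 split and exponential survival are assumed here.

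- Events, Schoenfeld: 4 × (1.960 + 0.842)² / (ln 1.23)² = 733. Freedman: (1.960 + 0.842)² × (2.23/0.23)² = 738.
- Ten-year death probability: 1 − 0.5^(10/6.2) = 0.673 in the reference group; 1 − 0.5^(1.23 × 10/6.2) = 0.747 at HR 1.23; mean 0.710.
- N: 738/0.710 gives 1,040 and 733/0.673 gives 1,090. Both are within 3% of the planned 1,070.

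The condition count appears nowhere in this calculation, so merging entries leaves N = 1,070 as it is.

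**2. The entry rule applied as printed.** Take a patient whose only listed disease is a stroke, recorded under both entries. The count is 2 and the patient qualifies. With the two entries merged the list has 39 entries, the count is 1 and the patient does not qualify.

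**3. How many patients this could affect.** The article gives no prevalences, so this is an illustration. Assume that conditions are independent and that every stroke is also recorded as cerebrovascular disease. The share of stroke patients with none of the other 38 conditions is then:

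- all 38 at the 5% floor in the entry criterion: 0.95^38 = 14%;
- hypertension at 30%, the other 37 at 5%: 0.70 × 0.95^37 = 10%;
- hypertension at 70%, the other 37 at 5%: 0.30 × 0.95^37 = 4.5%.

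Taking 2% as an assumed lower value, to allow for commoner or positively correlated conditions, and stroke prevalence of 5% to 20%:

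- low end: 1,070 × 0.05 × 0.02 ≈ 1 patient (0.1%);
- high end: 1,070 × 0.20 × 0.142 ≈ 30 patients (2.8%).

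**4. What the pair could do to the clusters.** Binary diagnoses were simulated for 1,070 patients and grouped by k-means into three clusters. The result is the highest minus the lowest stroke prevalence across clusters, in percentage points. All prevalences are assumptions. In the runs with independent conditions, ten other conditions ranged from 12% to 70%, and stroke and infarction were at 20% each. The columns give the share of strokes also recorded as cerebrovascular disease.

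| Set-up | No parent entry | 30% | 50% | 70% | 100% |
|---|---|---|---|---|---|
| Other conditions independent, stroke pair only | 11 | – | 71 | 92 | 92 |
| Genuine disease patterns present, stroke pair only | 4 | 9 | 65 | – | 91 |
| Genuine patterns present, infarction pair also double-recorded | 2–5 | 2–5 | 2–5 | 51 | 91 |

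A dash means that the set-up was not run at that value. In the third row the 2–5 covers runs at 20% to 50% double recording, which matched the run without parent entries. With complete double recording the artefact dominates in every set-up. At 30% it is small where genuine patterns exist. Around 50% the answer depends on the other structure in the data.

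**The case against.** The strongest reply is that the article does not say both entries reach the clustering. It refers only to the most frequent baseline diagnoses, and Strengths and limitations gives cancer, cardiovascular and neurological groups as examples, which suggests that related codes may be grouped first. Such mapping is commonly left to a full protocol or analysis plan, and neither is shown. This stands: a reader might infer that the clusters will reflect duplicate coding, but the document supports only that they could.

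A reader might also treat infarction and ischemic cardiomyopathy as a second duplicate pair. They are causally related, but either can occur without the other, so they do not occur together by definition. Counting a disease and its consequence separately is a choice of definition, and the Introduction notes that there is no consensus on how to make it. This stands too, and the point does not rely on that pair.

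The simulations depend on an unknown double-recording rate. The comparison without parent entries is also not a set of sound clusters: on independent data k-means still formed groups around the two commonest conditions, with spreads of 65 and 62 points. That limits the figures to showing what is possible.

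Finally, few hospitalized patients aged 65 or over are likely to have no other condition on such a long list. This is fair, and it is why the eligibility effect is rated as probably small.

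None of this removes the fault in the printed entry rule. ICD-10 supplies codes, not a rule for counting overlapping entries once.

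**Conclusion.** The point holds for stroke and cerebrovascular disease. The printed criterion lets one disease recorded twice count as multimorbidity, contrary to the article's own meaning of the term. The number of patients admitted in this way is probably small, 0.1% to 2.8% of the cohort if conditions are independent, every stroke is recorded twice and stroke prevalence is 5% to 20%.

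The clustering consequence is conditional. It needs both entries as inputs and a substantial double-recording rate. Where both apply it can dominate the result, with a spread of about 91 points against 4 without the parent entry when genuine patterns are present. It would then alter the secondary analyses built on multimorbidity patterns.

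A reader might infer that the main result is compromised. It is not: the association of Δage with mortality uses neither the condition count nor the clusters, and N = 1,070 is unchanged.

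**What to change.** Before the random selection in Phase II, state that stroke and cerebrovascular disease count as one condition for the entry rule, and that the single merged variable is the clustering input. Doing this before DNA extraction and the array assays matters, because a patient found ineligible afterwards is costly to replace.

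The cost is one sentence in the inclusion criteria, a recode of existing ICD-10 data, and the replacement of a few patients from the same database.

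Whether to merge infarction with ischemic cardiomyopathy is the sponsor's choice of definition. State the choice, and check its influence by repeating the clustering with the two merged.

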### Outcome variables

#### Overall mortality

Mortality data include the date, place, and causes of death (when available). Up to 10 years' information on survival status (i.e., dead or alive) will be obtained from the Marche Region's administrative database.

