#### CGA

CGA was conducted at admission and discharge using the validated interRAI Minimum Dataset for Acute Care (MDS-AC) (51), encompassing identification information, demographic data, functional state assessment, number and type of diagnoses, and number and type of medications, treatments, and procedures (50). Functional status was evaluated on the basis of several dimensions: the number of impaired basic and instrumental activities of daily living (BADL and IADL) (48, 52, 53) as a measure of functional status; the cognitive performance scale (CPS) as a measure of cognitive function; sensory functioning (hearing and vision); history of falls; pressure sores and skin conditions; pain; delirium, and behavioral changes; nutritional status and oral health; urinary incontinence; and, recent weight loss.

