## Strengths and limitations

This study will be able to rely on a comprehensive database containing clinical, functional, and biological information on more than 1,000 MM patients who have been monitored for 10 years. This project will highlight the most significant diagnostic and prognostic clinical, functional, and biological markers of MM, thereby recommending their implementation in clinical settings to identify those patients with a higher risk of death, hospitalization, or functional decline. Moreover, this study will enable the identification of those drug interactions that affect older adults. In parallel with patient involvement and empowerment, this study seeks to contribute to improvements in healthcare policies and their implementation in practice.

This study's additional strengths include: (i) the sample cohort composed of hospitalized patients over 65 years of age. For this reason, we expected to find higher mortality rates than those observed in a community-dwelling population. This should significantly reduce the number of censored observations and, consequently, the required sample size to detect these potential modifiers; (ii) the relatively long follow-up period that will allow us to adjust for several confounders and mitigate several sources of bias; (iii) clinical, functional, biological, and mortality data accuracy acquired over 10 years of monitoring; and iv) a dimensionality reduction approach that will be performed to decrease the number of variables by clustering patients into a few groups based on the MM pattern (i.e., cancer, cardiovascular, and neurological) or the functional status.

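### Entry is conditioned on information out to 10 years although recruitment ran to 2019: the criterion either excludes most of the cohort or, on one reading, admits recent recruits only if they have died

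*Protocol article*

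**What the plan says.** Protocol article, Phase II: Patient selection: 1,070 patients "will be randomly selected from the Reportage database on the basis of the following inclusion criteria". The fourth criterion is "Availability of information from baseline to 10 years of follow-up: death, hospitalization, clinical records, functional status"; it continues with routine laboratory values, new comorbidities after the first discharge, and drug intake.

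Study design: "The project began in September 2011" and "This study included patients who were recruited until 2019".

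Other sections treat 10 years as a ceiling. Phase I: "Follow-up information on the date of death will be provided for all Reportage project patients for up to 10 years". Overall mortality: "information on survival status (i.e., dead or alive) will be obtained from the Marche Region's administrative database", again with 10 years as the maximum. Study design (follow-up update) and Use of healthcare resources have the same sense. Strengths and limitations instead describes "more than 1,000 MM patients who have been monitored for 10 years".

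On function, the CGA section states: "CGA was conducted at admission and discharge using the validated interRAI Minimum Dataset for Acute Care (MDS-AC").

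No data cut-off date is given, and nothing says how a living patient with less than 10 years is handled at selection.

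**The concern.** Eligibility for a survival analysis should be decided from what is known at baseline. This criterion looks forward. Phase I updates the dates of death before Phase II selects patients, so vital status is already known when eligibility is judged. Patients recruited in 2019 cannot be seen alive at 10 years before 2029, and at the ethics approval dated 04/02/2021 no recruit had 10 years.

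At stake are the Cox hazard ratio for Δage, the Kaplan-Meier curves and Harrell's C. If selection depends on having died, a larger sample does not help, and no later analysis can restore patients who were never drawn.

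A smaller fault lies in the same criterion. It asks for functional status out to 10 years, but the functional assessment is described only at admission and discharge. The regional database is named for survival and healthcare use, not for function.

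**Working it through.** **Inputs from the article.** Sample size: N = 1,070, HR 1.23, α = 0.05, β = 0.2, 10 years, reference median 6.2 years. Statistical analysis: two-tailed test, Cox model. Study design: recruitment September 2011 to 2019.

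**Assumptions, not in the article.** Exponential survival, two equal groups, no dropout, uniform recruitment to the end of 2019, cut-offs at the start of 2022, 2023 and 2024.

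**The plan's own figure.** Hazard = ln 2/6.2. Deaths by 10 years: 1 − exp(−10 × ln 2/6.2) = 67.3% in the reference group and 1 − exp(−12.3 × ln 2/6.2) = 74.7% in the other, mean 71.0%.
- Schoenfeld: 4 × (1.960 + 0.842)²/(ln 1.23)² = 733 deaths; 733/0.710 ≈ 1,033 patients.
- Freedman: (1.960 + 0.842)² × (2.23/0.23)² = 738 deaths; 738/0.710 ≈ 1,040 patients, within 3% of 1,070.
- Power at 1,070 (760 deaths): Φ(0.2070 × √(760/4) − 1.960) = 81%.

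The stated size is reproduced, but only if every patient has 10 possible years of follow-up.

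**Share of recruits with 10 possible years.** Recruitment lasts 8.33 years. At the three cut-offs, 0.33, 1.33 and 2.33 years of intake are at least 10 years old: 0.33/8.33 = 4%, 1.33/8.33 = 16%, 2.33/8.33 = 28%.

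**Three ways to apply the criterion.** I simulated 3,000,000 patients with a true HR of 1.23. Power = Φ(ln HR × √(d/4) − 1.960), with d = 1,070 × share dead.

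| Reading | Quantity | 2022 | 2023 | 2024 |
|---|---|---|---|---|
| A. Living patients with under 10 years admitted and censored | HR | 1.23 | 1.23 | 1.23 |
| | Share dead | 51% | 57% | 61% |
| | Power | 68% | 72% | 75% |
| B. 10 possible years required, dead or alive | HR | 1.23 | 1.23 | 1.23 |
| | Recruits eligible | 4% | 16% | 28% |
| | Power if 1,070 can be found | 81% | 81% | 81% |
| C. Died, or has 10 possible years | HR | 1.082 | 1.127 | 1.154 |
| | Share dead | 98% | 92% | 88% |
| | Recent recruits (all dead) in sample | 92% | 74% | 60% |
| | Reference median, years (true 6.2) | 2.5 | 3.1 | 3.6 |
| | Power | 25% | 47% | 59% |

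Worked case, C in 2023: 1,070 × 0.924 = 989 deaths; 0.1196 × √(989/4) = 1.880; Φ(1.880 − 1.960) = 47%. Worked case, A in 2023: 1,070 × 0.567 = 607 deaths; 0.2070 × √(607/4) = 2.550; Φ(0.590) = 72%. Separate simulation runs gave 25%/48%/58% for C and 68%/71%/76% for A, the same within about a point.

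Under C the ratio shrinks because recent recruits in both groups are all dead by construction. Only the timing of death inside a short window can still differ between the groups.

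**Feasibility under B.** Finding 1,070 patients needs at least 1,070/0.04 = 26,750, 1,070/0.16 ≈ 6,690 or 1,070/0.28 ≈ 3,820 recruits, before the multimorbidity and sample criteria are applied. The article does not give Reportage's total.

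**Partial application.** If half of the living patients with short follow-up are admitted, the HR is about 1.19 to 1.21 for cut-offs from 2021 to 2025. If all are admitted, it is 1.23.

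**The case against.** A reader might infer that the plan does select on death and that its primary hazard ratio will therefore be biased. The article does not support that. Only reading C produces the shrinkage, and the article nowhere says that a death completes the record while a living patient with shorter follow-up is dropped. Five places give 10 years as a maximum (the Abstract's Methods, Study design, Phase I, Overall mortality, Use of healthcare resources). Strengths and limitations expects fewer censored observations, so it foresees some. This is a fair case for reading A, and it means the bias must be stated as conditional.

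The criterion may also have a benign purpose. Reportage recruited in four cities, while survival and healthcare use come from one region's database. Requiring that records can be linked is legitimate and should be kept.

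A second tempting inference is that asking about comorbidity onset after first discharge removes in-hospital deaths. It does not follow: the criterion asks for information on onset, not for survival to discharge, and a patient who died in hospital has a complete record.

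Nor is the whole loss of power under C due to the filter. Staggered entry alone brings 1,070 patients below 80% under reading A.

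What the objection does not remove: the ceiling wording describes the follow-up to be obtained, whereas the criterion alone governs entry and runs to 10 years. The statement that patients were followed for 10 years points the same way. The sections conflict on who enters the primary analysis.

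**Conclusion.** The point holds as a conflict in the entry rule that must be settled before sampling. Applied as written, the criterion has two outcomes:
- Most of the cohort is ineligible: about 4%/16%/28% qualify at 2022/2023/2024 cut-offs, with the HR unbiased.
- If death counts as complete information, recent recruits enter only when dead. The HR falls from 1.23 to about 1.08/1.13/1.15, and power at 1,070 to about 25%, 47–48% and 58–59%.

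If the ceiling wording governs and survivors are censored, there is no bias. The shrinkage is therefore conditional on the reading, and its size on the unstated cut-off date, uniform recruitment and exponential hazards. The sample-size arithmetic is not wrong in itself; it assumes 10 possible years for everyone, which recruitment to 2019 does not give at these cut-offs. The mismatch over functional status stands without any such assumption.

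**What to change.** Before the random draw, replace the fourth criterion with baseline-only eligibility: age, two or more listed conditions, baseline data, stored buffy coat and plasma, and linkability to the regional database. Follow every selected patient from admission to death, loss of linkage or one stated administrative censoring date, to a maximum of 10 years. Align Phase II and Strengths and limitations with the sections that treat 10 years as a ceiling.

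Alternatively, restrict by admission date (at least 10 years before the cut-off) regardless of vital status. This is also unbiased and keeps the planned power, but only if enough patients were recruited that early.

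Define separate analysis sets for outcomes that need later data. Limit functional change to admission-to-discharge unless a later source is named.

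The cost is a wording change and, with censoring, fewer deaths per patient. The stated 80% power should be restated: about 68%, 71–72% and 75–76% at N = 1,070 for 2022/2023/2024 cut-offs under the assumptions above. A later cut-off or a larger sample would recover it.
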